### Participants

Participants will be 50 patients with ADHD. Patients will be recruited from Imam-Hossein psychological services center affiliated with Shahid Sadoughi University of Medical Sciences, Yazd, Iran. The inclusion criteria will be as follows: age 7–13 years, ADHD diagnosed by a psychiatrist, IQ higher than 80, theta brain waves higher than 7 Hz, beta brain waves lower than 13 Hz, increasing theta/beta power ratio in frontal, temporal and central electrode sites, resident of Yazd city, and informed consent signed by one of the patient’s parents. Exclusion criteria will be as follows: other psychotic diseases, taking any medication for ADHD during the past year, hormonal disorders including Addison's disease, Cushing syndrome, hyperparathyroidism, hypo- and hyperthyroidism, chronic diseases such as cancer, diabetes, stroke, kidney disease, liver disease, multiple sclerosis, fibromyalgia, and Parkinson’s disease, addiction of parents to alcohol/drugs at the time of the child’s birth, adherence to any specific diet in the past year, taking multivitamins or mineral supplements more than twice a month in the last 6 months, being on a special diet during the past year, and unwillingness to continue the study. We measured serum concentration of vitamin D before study. This study will be conducted among patients with ADHD who have vitamin D deficiency and vitamin D insufficiency.

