### Adherence

Vitamin D and placebo boxes will be given to participants at weeks 0 and 4. Participants will be asked to return the boxes with their remaining contents at the end of every 4 weeks, and any occurrence of adverse events will be recorded. To evaluate the compliance rate, the consumption of vitamin D and placebo will be monitored at the end of each 4 weeks of intervention. At the end of intervention, the remaining contents of bottles will be recorded for each participant. Consuming less than 80% of the administered vitamin D or placebo will be defined as poor compliance. Participants with poor compliance will be excluded from study and their data will not be analyzed at the end of the study. After the study, the participant’s results will be provided to the participant's parents. Before the final data collection, parents will be contacted by phone to remind them. Participants can leave the study for any reason at any time. The investigator can withdraw participants from the trial (after consultation with the protocol chair and ethical committee) in order to protect the safety of participants or if they are unwilling or unable to continue the study. All randomized participants who are discontinued from study will follow the same schedule of events as those participants who continue the study except adherence assessment.

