#### Statistical analysis

SPSS version 24 (SPSS, Inc.) will be used for data analysis. The analyses will be performed using the intention-to-treat (ITT) approaches. Using Kolmogorov-Smirnov test, normal distribution of variables will be assessed. Comparing the qualitative variables between two groups will be performed using chi-squared test. To compare the means of normal variables at baseline, at the end of study, and compare the mean changes of normal data between two groups, independent *t*-test will be used. To compare normal variables within the groups, paired sample *t*-test will be applied. Using Mann-Whitney *U* test, comparing abnormal data between the two groups at baseline and after the intervention as well as comparing the mean changes of abnormal data between two groups will be performed. Wilcoxon test will be used to compare the abnormal data within the groups. To control covariates, ANCOVA will be carried out. *P* < 0.05 will be considered significant.

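### Unwillingness to continue, a post-entry event, is listed as an exclusion criterion; this conflicts with the Adherence section and with intention-to-treat, and no rule says which governs

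*Protocol article*

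**What the plan says.** All references are to the protocol article.

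- **Participants.** The exclusion criteria close with "being on a special diet during the past year, and unwillingness to continue the study". The section does not say whether the last item applies before or after randomisation, or what happens to the data of a child who meets it.
- **Adherence, leaving.** "Participants can leave the study for any reason at any time".
- **Adherence, withdrawal.** After consulting the protocol chair and the ethical committee, the investigator can withdraw participants "in order to protect the safety of participants or if they are unwilling or unable to continue the study".
- **Adherence, follow-up.** "All randomized participants who are discontinued from study will follow the same schedule of events as those participants who continue the study except adherence assessment".
- **Adherence, compliance.** Taking less than 80% of the capsules is poor compliance, and "Participants with poor compliance will be excluded from study and their data will not be analyzed at the end of the study".
- **Statistical analysis.** "The analyses will be performed using the intention-to-treat (ITT) approaches". The section does not define the analysed set further.

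**The concern.** One event, a family that no longer wants to go on, is covered by several rules with different consequences for the data. Under the exclusion criterion the child can be treated as outside the trial. Under the right to leave, nothing further need be collected. Under the follow-up sentence, the week-8 Conners' parent rating, EEG and blood sample are still due. The Adherence section uses one expression both for stopping capsules and for leaving follow-up, and a child who has really left cannot keep to the schedule.

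The comparison of randomised groups is at stake. Families may stop because the child is doing badly or because they see no benefit, and that can differ by arm. A criterion that a post-randomisation event can trigger lets such children be set aside on grounds related to outcome. It also weakens the one sentence in the article that protects against missing week-8 outcomes.

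**Working it through.** **1. When can the criterion act?** Refusal at entry is already covered twice: signed parental consent is an inclusion criterion (Participants), and the Sample size section admits only those willing to take part. What remains is a change of mind after consent. Part of that is harmless (a family that consents, is screened and declines before randomisation), but the text does not limit the criterion to that interval. It therefore also reaches randomised children.

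**2. What does exclusion mean here?** The only place where the article gives a consequence for excluding a participant is the compliance rule, where exclusion and non-analysis stand in one sentence. A site or analyst who reads the two sections together has a written precedent for dropping quitters. The follow-up sentence and the intention-to-treat statement point the other way. The article gives no order of precedence.

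**3. Which children does it affect beyond the 80% rule?** The course is 8 weekly capsules, in boxes of 4 given at weeks 0 and 4 (Intervention, Adherence). 80% of 8 is 6.4, so 7 capsules are needed: 7/8 = 87.5%, while 6/8 = 75%.

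| Child | Share taken | 80% rule | Exclusion criterion |
|---|---|---|---|
| Stops in week 3, at most 3 capsules | 3/8 = 37.5%; 3/4 of first box = 75% | Already removed on either count | Adds nothing |
| Finishes first box, leaves at week 4 | 4/4 = 100% of dispensed; 4/8 = 50% of course | Depends on the denominator | May decide the outcome |
| Takes 7 capsules, declines week 8 | 7/8 = 87.5% | Passes | May decide the outcome |

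Most early quitters thus fall under the compliance rule as well. The criterion matters by itself mainly for late quitters and, on one reading of the denominator, for those who leave after the first box.

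**4. The plan's own figure.** The Sample size section gives 25 per group after about 10% drop-out, but no means or SD, so the core calculation cannot be reproduced. The drop-out step is consistent with a base of 22 per group: 22/0.90 = 24.4, rounded up to 25. A base of 23 would give 23/0.90 = 25.6, rounded up to 26. The planned loss is 10% of 50, or about 5 children.

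**5. Size of a possible bias.** If a share q of one arm is lost and those children differ from the rest of that arm by g SD, the mean of those who remain moves by q × g. The values of q and g below are assumptions, except that 10% is the plan's general drop-out allowance.

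- q = 10%, g = 0.5 SD: 0.05 SD.
- q = 20%, g = 0.5 SD: 0.10 SD. The same shift follows from q = 10%, g = 1 SD.
- Exactly the worst-scoring 10% of one arm lost, normal scores, leavers in the other arm random: φ(1.2816)/0.90 = 0.1755/0.90 = 0.195 SD.

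For scale, the plan's formula with 25 × 0.90 = 22.5 analysable children per arm gives a detectable difference of (1.96 + 0.8416) × √(2/22.5) = 0.835 SD. This is back-calculated and is not stated in the article. The ratio 0.195/0.835 is 23%. The direction depends on which arm loses its worst-scoring children.

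**The case against.** The strongest reply is that this is one misplaced phrase. The Participants section says nothing of randomised children, removal of data or non-analysis. The Adherence section speaks specifically of all randomised participants, and a specific rule ordinarily prevails over a loosely worded list item. Intention-to-treat is stated. The right to leave is a standard ethical statement and can coexist with continued follow-up. The article also condenses a full protocol that is not shown and that may define the terms.

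Much of this stands. A reader might infer that the plan orders quitters to be removed as ineligible. It does not: removal is a risk that the text permits. A reader might also infer that the investigator must withdraw an unwilling child, or that follow-up after discontinuation is complete. The article says only that the investigator can withdraw, and it exempts the adherence assessment. Nor is the problem wholly separate from the 80% rule, as the table of cases shows.

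The reply does not remove the conflict. The criterion and the sentences that it contradicts are all stated text, so this is not a detail left to a fuller document. The intention-to-treat sentence cannot settle the matter, because the article already departs from it for poor compliers.

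**Conclusion.** The point holds as a contradiction in stated text: a post-entry event serves as an exclusion criterion, the same event is handled otherwise under Adherence, and nothing says which rule applies to a randomised child. The consequence is a permitted loss of outcomes, not a prescribed one.

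Its size cannot be derived from the document. It is tempting to say that the flaw is worth 23% of the target effect. The article does not support this: that figure charges the whole 10% drop-out allowance to one phrase, assumes that exactly the worst-scoring children of a single arm leave, and compares the result with a target that the article does not state. It is an upper illustration for a 10% loss. The milder values rest equally on assumed inputs. Nor would the correction recover all of the loss, because children whose families refuse follow-up still give no week-8 data. The case for correction rests on the conflict and on the low cost of resolving it.

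**What to change.** 1. **Participants.** Delete the item on unwillingness to continue from the exclusion criteria, or reword it so that it applies only before randomisation.
2. **Adherence.** Separate two events. After a child stops capsules, the week-8 Conners' parent rating, EEG and blood sample are still sought. After consent to follow-up is withdrawn, nothing more is collected, but data to date are kept in the randomised arm. Limit the same-schedule sentence to the first event, and record date and reason for each.
3. **Compliance rule.** Reconcile the 80% exclusion with intention-to-treat in the same amendment. Otherwise most early quitters remain outside the analysis whatever is done under items 1 and 2.

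These changes concern data collection and the analysed set; they set no clinical rule on stopping treatment. The cost is a wording amendment, ethics committee approval where the article requires it, and one status form. No visits are added, because the article already schedules the assessments.

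The Trial status section expected recruitment to end on 30 August 2021, and the article appeared in October 2022. If enrolment is complete, missed visits may not be recoverable. The fix then applies to the analysis set and the reporting: keep every randomised child in the assigned arm, use the data already collected, and report the date and reason for each departure by arm.

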### Ethics and trial registration

Participants and their parents will be notified about the risks and advantages of the present study, and then the investigator will ask them to sign an informed written consent. The study protocol and informed written consent are approved by the ethical committee of Shahid Sadoughi University of Medical Sciences and Health Services in Yazd, Iran (there are two theses with code number: IR.SSU.SPH.REC.1400.028 and also code number: IR.SSU.SPH.REC.1395.97). Any changes in the protocol that may affect the implementation of the study, including changes in study objectives, study design, participant population, sample size, and study procedures must be approved by the ethical committee of Shahid Sadoughi University of Medical Sciences and Health Services to be applicable. Before conducting a possible ancillary study, the approval of the ethics committee as well as the informed written consent of all participants will be obtained. Additional serum samples will be stored for use in future studies. The Shahid Sadoughi University of Medical Sciences will pay for the treatment of immediate adverse events related to study procedures. The registration of the study protocol was performed at the Iranian Registry of Clinical Trials with code number website, under code number IRCT20200922048802N1 with URL: https://www.irct.ir/trial/51410.

### ADHD diagnosis

According to the Diagnostic and Text Revision of Statistical Manual of Mental Disorders-Fifth Edition (DSM-V) [47, 48], the diagnosis of ADHD will be done by a psychiatrist. Based on the DSM-V criteria, a person who has at least six of the listed symptoms of inattention or symptoms of hyperactivity–impulsivity persisting for at least 6 months which are disruptive and inappropriate for the person’s developmental level is defined as a patient with ADHD [47, 48].

### Sample size

Sample size is calculated based on means and standard deviations for Conners’ ADHD Index, as the primary outcome of the study of Gow et al. [49] by considering 95% confidence interval, 80% power (*α* = 0.05 and *β* = 0.2), and using the following formula:$$n=\frac{{\left(\textrm{z}\frac{\alpha }{2}+\textrm{z}\upbeta \right)}^2\times 2{S}^2\ }{{\left(x1-x2\right)}^2}$$

Considering a drop-out rate of approximately 10%, the final sample size needed was estimated to be 25 per group. All participants will be included in the RCT if they meet the inclusion criteria and are willing to participate in the study, until the estimated sample size is completed.

### Randomization and blinding

Simple (unrestricted) randomization will be performed, and participants will be divided randomly into two groups including intervention (vitamin D, *n* = 25) and control (placebo, *n* = 25) by a person who is not involved in the trial using the computer-generated random number table (produced by random allocation software) [50]. Concealing allocation sequence from those assigning participants to the intervention groups will be performed utilizing opaque sealed envelopes. Boxes of vitamin D or placebo will be named as A and B by a third person that is not involved in the study. Participants, investigators, and laboratory staff will be blinded to the treatment allocation. Randomization codes will be unlocked only after all patients complete the study protocol.

### Intervention

The intervention group will receive one capsule 50,000 IU vitamin D every week, for 8 weeks. The control group will receive one placebo capsule containing 1000 mg olive oil every week. Preparing placebo in the same appearance, taste, and color as the vitamin D will be performed by the Pharmacy Faculty of Shahid Sadoughi University of Medical Sciences. Participants will not receive any medication for ADHD during follow-up. Vitamin D and placebo will be packed in boxes with the same color, shape, and size. A person who is unaware about the trial details will label the boxes containing vitamin D and placebo as A or B. To preserve the blindness in case of serious adverse events, the third party will use unique codes. Every 4 weeks, the participants will receive the boxes of capsules. Each box contains 4 capsules (providing one capsule per week for 4 weeks). Participants must consume the contents of each box within 4 weeks. At the end of the study, the person who will label the boxes will inform the researchers about details of labeling.

### Adherence

Vitamin D and placebo boxes will be given to participants at weeks 0 and 4. Participants will be asked to return the boxes with their remaining contents at the end of every 4 weeks, and any occurrence of adverse events will be recorded. To evaluate the compliance rate, the consumption of vitamin D and placebo will be monitored at the end of each 4 weeks of intervention. At the end of intervention, the remaining contents of bottles will be recorded for each participant. Consuming less than 80% of the administered vitamin D or placebo will be defined as poor compliance. Participants with poor compliance will be excluded from study and their data will not be analyzed at the end of the study. After the study, the participant’s results will be provided to the participant's parents. Before the final data collection, parents will be contacted by phone to remind them. Participants can leave the study for any reason at any time. The investigator can withdraw participants from the trial (after consultation with the protocol chair and ethical committee) in order to protect the safety of participants or if they are unwilling or unable to continue the study. All randomized participants who are discontinued from study will follow the same schedule of events as those participants who continue the study except adherence assessment.

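### The protocol declares intention-to-treat but also bars children who take under 80% of capsules from the analysis; the two rules conflict, and the second, if applied, gives a per-protocol comparison

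*Protocol article*

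**What the plan says.** Three statements in the protocol article decide who is analysed.

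- Statistical analysis: "The analyses will be performed using the intention-to-treat (ITT) approaches". No other analysis population is named.
- Adherence, definition: "Consuming less than 80% of the administered vitamin D or placebo will be defined as poor compliance". Adherence, consequence: "Participants with poor compliance will be excluded from study and their data will not be analyzed at the end of the study".
- Adherence, last sentence: "All randomized participants who are discontinued from study will follow the same schedule of events as those participants who continue the study except adherence assessment".

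The number of capsules comes from the Intervention section: "The intervention group will receive one capsule 50,000 IU vitamin D every week, for 8 weeks". The placebo arm also takes one capsule a week, and the same cut applies to both arms.

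**The concern.** Intention-to-treat keeps every randomised child in the allocated arm, whatever the child took. The Adherence rule removes randomised children on the strength of a capsule count observed after allocation. What remains is an adherence-defined set, usually called per-protocol.

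Capsule-taking in this age group can depend on symptom severity, family functioning, side effects or perceived lack of benefit. The symptom outcome is a parent rating, and parents plausibly influence whether capsules are taken. Adherence and outcome may therefore be linked, and the link may differ between arms. If it does, the randomised comparison is no longer protected. A reader of the results, seeing intention-to-treat in the methods, would not know it.

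**Working it through.** **1. The rules side by side.**

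| Question | Statistical analysis | Adherence |
|---|---|---|
| Is a child with under 80% of capsules analysed? | Yes, implied by intention-to-treat | No, stated outright |
| Is such a child followed to week 8? | Not addressed | Excluded from the study, yet discontinued participants keep the schedule |
| Which rule prevails? | Not stated | Not stated |

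The first row is a direct contradiction. An analysis plan could follow one section only by breaching the other. The second row is an ambiguity: the follow-up sentence comes after the rules on leaving and withdrawal, and the article does not say whether it covers children excluded for poor compliance.

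**2. Where the cut falls.** Capsules: 1 per week × 8 weeks = 8. Cut: 0.80 × 8 = 6.4. Seven taken is 7/8 = 87.5% and passes; six taken is 6/8 = 75% and fails. Two missed capsules remove a child.

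**3. How many children that could be.** The article gives no expected adherence, so this rests on an assumption: each capsule is missed independently with probability p.

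P(at least 2 of 8 missed) = 1 − (1−p)^8 − 8p(1−p)^7

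- p = 0.05: 1 − 0.663 − 0.279 = 0.057, or 5.7%
- p = 0.10: 1 − 0.430 − 0.383 = 0.187, or 18.7%

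The rule could therefore affect anything from a child or two per arm (0.057 × 25 = 1.4) to four or five (0.187 × 25 = 4.7).

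**4. What selective removal could do.** Assumptions: no true effect, 25 per arm, a fraction f removed from one arm only, and removed children m SD worse than that arm's average. The retained mean then shifts by f × m / (1 − f). The standard error in SD units is √(1/(25(1−f)) + 1/25), and the type I error is for a nominal two-sided 5% test.

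| f | m | Shift (SD) | Type I error |
|---|---|---|---|
| 0.10 | 0.5 | 0.05/0.90 = 0.056 | 0.054 |
| 0.10 | 1.0 | 0.10/0.90 = 0.111 | 0.067 |
| 0.20 | 0.5 | 0.10/0.80 = 0.125 | 0.070 |
| 0.20 | 1.0 | 0.20/0.80 = 0.250 | 0.133 |

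These are extreme in one respect: all removals are in one arm. Equal removals for the same reasons in both arms would give little bias.

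**5. Does power argue for the change?** The planned 25 per group cannot be reproduced, because the Sample size section gives no means or SD. Working backwards, 22/0.9 = 24.4, rounded up to 25, and 22 per group under the stated formula implies a standardised difference of (1.96 + 0.84) × √(2/22) = 0.845. Take that as an assumption, with 25 × 0.9 = 22.5 per arm after drop-out and 18.7% poor compliers (two-sample t-test):

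- excluding them: 22.5 × 0.813 = 18.3 per arm, power 70%
- including them, half the effect in poor compliers: 0.845 × (1 − 0.187 × 0.5) = 0.766, power 71%
- including them, no effect in poor compliers: 0.845 × 0.813 = 0.687, power 62%

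Power does not clearly favour either rule.

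**The case against.** The strongest reply is that the article declares intention-to-treat and nothing shows that the exclusion will override it. That stands as far as it goes: what is shown is an unresolved contradiction, not a settled per-protocol analysis. It does not remove the problem, because the exclusion is equally definite and is not confined to a secondary set.

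The second reply is that participants and investigators are blinded, the placebo matches in appearance, taste and colour, and one cut applies to both arms. This also stands: a large imbalance in exclusions is less likely than in an open trial. Blinding does not guarantee that adherence is balanced, or that the children removed from each arm are alike.

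Three stronger readings are tempting and should not be drawn.

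- A reader might apply the 80% cut to each four-capsule box, so that a single missed capsule removes a child. The four-weekly check is described as monitoring, while remaining contents are recorded at the end of the intervention and data are withheld at the end of the study. One cut over all eight capsules is the more natural reading.
- A reader might infer that the exclusions cost the trial its planned power. The effect size and miss rates are not in the article. The Sample size section says only "Considering a drop-out rate of approximately 10%, the final sample size needed was estimated to be 25 per group" and does not define drop-out, so poor compliers may already be counted there. If a 5.7% exclusion were the only loss, 25 × 0.943 = 23.6 per arm would remain, with about 81% power at the back-calculated difference.
- A reader might infer that outcomes of the excluded children are certain to be collected. The follow-up sentence speaks of discontinued participants, and participants may leave at any time.

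**Conclusion.** The contradiction is real and explicit in the current text, and it concerns who enters the primary comparison, so it must be resolved. If the Adherence rule is applied, the main result is a per-protocol comparison selected on a post-randomisation variable, under an intention-to-treat label.

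That conclusion needs no assumption beyond the article's wording. The share of children affected and the shift in the estimate do: the article supplies neither adherence rates nor outcomes by adherence, so the direction of the bias is unknown and the 0.06 to 0.25 SD range is illustration only. The case rests on keeping the randomised comparison intact, not on power.

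**What to change.** In Adherence, delete the rule that data of poorly compliant children are not analysed. State instead that their outcomes are collected where available, and make explicit that the follow-up sentence for discontinued participants covers them. In Statistical analysis, state that the primary analysis includes these children in the arm to which they were randomised. Keep children with at least 80% compliance, defined once over all eight capsules, as a labelled sensitivity set.

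Recruitment was expected to end on 30 August 2021 and the article appeared in October 2022, so follow-up may be over. In that case, apply the rule to all outcome data already collected and report how many poorly compliant children in each arm have none.

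The change affects outcome collection and analysis only; it does not touch dose, schedule or decisions about stopping treatment. The cost is wording, plus some dilution of the estimate by non-adherence, which may lower power. Week-8 outcomes cannot be guaranteed for every child, so some values may still be missing.
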